### 2.8. Clinical History and Blood Tests

Sociodemographic (age, sex, education level, healthcare reference area, working situation), and clinical variables are recorded. A clinical history, physical examination and basic blood tests are performed. Blood pressure is measured after 5 min in the sitting position with a manual sphygmomanometer, adapted to the size of the patient’s arm. HbA1c is measured by HLPC, standardized against DCCT-IFCC. Glucose, total cholesterol, triglyceride, HDL cholesterol, AST, ALT, GGT, and creatinine are measured by automated, colourimetric methods. LDL cholesterol and glomerular filtration rates are calculated. Drug treatment is obtained from the interview and the electronic prescription.

Dyslipidaemia is defined by an LDL cholesterol above 160 mg/dL, triglyceride above 200 mg/dL or lipid-lowering drug treatment. Diabetes is defined by the American Diabetes Association criteria [47] or the need for glucose-lowering treatment. Hypertension is defined by blood pressure ≥140/90 mmHg or blood-pressure-lowering treatment. In women, hirsutism is defined by a score >8 points on the Ferriman–Gallwey scale. Chronic venous insufficiency is recorded if the diagnosis is present in the patient’s clinical records or is evident at physical examination. Other comorbidities associated with obesity, such as infertility, nonalcoholic fatty liver disease (NAFLD), gastroesophageal reflux or hiatal hernia, bronchial asthma, function limiting osteoarthritis, or intracranial hypertension are recorded if a previous diagnosis has been made.

### 2.9. Body Composition

Body composition is assessed at the baseline visit. Weight is assessed with a calibrated bioimpedance (*Tanita BC 420 MA III*, Tokyo, Japan) to the nearest 0.1 kg, and height, using a stadiometer to the nearest 0.5 cm, without shoes and with light clothing. Body Mass Index (BMI) is then calculated as weight (in kg) divided by height (in meters)^2^. Body composition is analyzed through Vectorial Bioimpedance by tetrapolar impedance plethysmography using an electric alternating current flux of 400 µA at an operating single sinusoidal frequency of 50 kHz (*Nutrilab™*, Akern, Firenze, Italy in resting conditions. Standard whole-body measurements are performed according to the manufacturer’s guidelines on the right side of the body with the subjects in supine position with their arms and legs abducted, and the skin cleaned to ensure good contact. The thighs are checked not to be in contact with each other and the arms not to be touching the sides of the body. Electrodes are placed on a line between the radial and ulnar styloid processes on the dorsum of the wrist and on a line between the medial and lateral malleoli on the dorsum of the ipsilateral foot, overlying the head of the third metacarpal on the dorsum of the hand and the third metatarsal on the dorsum of the foot. Total body water, fat-free mass, fat-free mass percentage, fat mass, fat mass percentage and body cell mass are determined according to the formulas of Kotler et al. [48], and bioelectrical parameters of resistance, reactance, and phase angle are registered.

### 2.10. Questionnaires

A series of self-completed questionnaires are completed before the first group session and after the last one. General health-related quality of life is assessed using the Spanish version of EuroQol-5D-5L (EQ-5D-5L) [49]. Dietary habits are explored using the Adherence to the Mediterranean Diet Adherence Screener (MEDAS) questionnaire [50], eating disorders, by means of the Spanish version of the Eating Disorder Inventory (EDI-3) [51,52], and anxiety and depression, using the Spanish version of the Hospital Anxiety and Depression Scale (HADS) [53,54].

### 2.11. Functional Tests

Six-minute walk test (6MWT): This is a cheap and easy to perform, submaximal stress test. Its aim is to cover the maximal distance in 6 min, walking on a flat surface, following a standardized protocol [55]. The patient is not coached nor stimulated to walk quickly, and he/she can stop and rest as needed. Blood pressure (beginning and end), heart rate (every minute), oxygen saturation (every minute), and self-perceived exertion (Borg, beginning and end). The percentage of the theoretical 6MWT distance (6MWD) is calculated using Enright’s regression equation [56].Handgrip strength (HGS) is measured in both hands with a classical, analogic hand dynamometre (0–90 kg, 0–200 Lb) (*JAMAR™* Hydraulic Hand Dynamometer, Preston, Jackson, Missouri, EEUU) following the protocol described by the American Society of Hand Therapists [57], with the patient seated, back and feet resting, shoulders adducted, elbow at 90°, and forearm and wrist in a neutral position. Three 3-s alternating measurements are performed on each hand and the average is calculated and the dominant hand is registered.Pulmonary function tests are performed according to the European Respiratory Society (ERS), American Thoracic Society (ATS) and Spanish Society of Pneumology and Thoracic Surgery (SEPAR) technical standards [58,59], by trained staff with a *MasterScreen*, Jaeger, Germany. Forced spirometry is performed under basal conditions, to assess respiratory capacity, maximal inspiratory pressure, and maximal expiratory pressure are measured at baseline. Plethysmography is used to measure pulmonary volumes, residual volume and functional residual capacity. Pulmonary diffusion (DLCO) is assessed by gas dilution. Baseline arterial gasometry is also performed.Obstructive Sleep Apnea (OSA) is assessed during sleep by means of home cardio-respiratory polygraphy (*Somnoscreen™*, Sanro, Madrid, Spain), which is then interpreted manually by trained medical staff at the Sleep Unit, following SEPAR and American Academy of Sleep Medicine guidelines [60,61].

### 2.12. Adherence to the Intervention and Physical Activity

Adherence to the intervention is assessed by the attendance at the sessions. Physical activity is monitored using an activity app (*Google Fit* or the manager of an activity tracker) downloaded on a smartphone, as well as the Spanish short version of the International Physical Activity Questionnaire [62].

### 2.13. Monitoring and Follow-Up

Adverse events are registered and classified according to their intensity, severity and potential association with the intervention. In addition, halfway through the intervention (for session 4), participants with hypertension and diabetes are asked to monitor blood pressure and glucose concentrations, respectively. The registers are assessed by one of the endocrinologists, in order to reduce blood pressure and/or glucose-lowering drugs, when needed. These changes are registered.

### 2.14. Surgery

Information about the date, surgical procedure (including Foucher, staple size and type, gastric pouch size, gastrojejunal anastomosis diameter, common channel length), length of hospital stay, and early (first 30 days) complications are obtained from the participant’s clinical record. Post-operative complications are classified according to the Clavien–Dindo classification [63].

### 2.15. Statistical Analyses

At the time of the design of the protocol, we estimated that, during one year, we would be able to include 80 participants, 40 in each treatment arm, following two 10 person groups (one control and one intervention) at a time. The inclusion of 80 participants, without any loss to follow-up, assuming a standard deviation in weight of 11 kg [16], for a two-tailed *p* < 0.05, would allow a difference between groups, with 80–90% statistical power, of 8 and 7 kg to be detected, respectively. Assuming a standard deviation of 6 kg, as shown by other studies [64], the detectable difference would be reduced to around 4 kg.

A baseline descriptive analysis is performed, and variables are expressed as percentages, mean (SD) or median (interquartile range), as appropriate according to their type and distribution. Treatment groups are compared using chi-squared, Student’s *t* or Mann–Whitney’s *U*. Analyses will be performed by intention to treat. Missing values will be imputed using the last observation carried forward.

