### 2.3. Randomization and Allocation Masking

Participants are assigned to their treatment group (ratio 1:1) following a computer-generated random sequence. The latter is generated by a lab technician otherwise not involved in the trial. It is transferred to individual cards, which are inserted into opaque, sealed, consecutively numbered envelopes. When the participant signs the consent form and eligibility is confirmed, the first sealed envelope is opened to reveal the treatment group, and the patient is scheduled for the baseline assessment tests and the eight fortnightly sessions.

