### 2.5. Standard Treatment

The standard treatment (control group) consists of a structured, educational, and behavioural programme of eight 2-h, fortnightly sessions, followed by 1-h monthly sessions until surgery. Table 1 describes the contents of the sessions.

At the first session, all participants are given the contents of the education programme in writing and are asked (and trained) to start recording their physical activity by means of a free, mobile app (*Google Fit*) downloaded in their smartphones or an activity tracker, if they owned one, for motivation and monitoring of adherence. To avoid contamination between treatment arms, the control and intervention groups are scheduled every other week.

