## 3. Results

Participants in the pilot study had their first visit between 8 August 2019 and 13 September 2019, and the interventions took place between October 2019 and January 2020. 

Out of the 51 patients on the waiting list, expected to be operated on at least 4 months after recruitment, 19 accepted to participate. The main reasons given for declining were participation in preoperative groups in another centre (on a different island), distance to the training site and schedule problems, mainly due to working hours. None of the patients refused to participate or was excluded due to linguistic barriers. A total of 15 (14 women) attended the first visit and were randomized. Their mean age was 40.0 ± 10.0 years, baseline BMI, 46.7 ± 5.9 kg/m^2^, and waist circumference 134.2 ± 12.0 cm. The most frequent complications of obesity were OSA (54%), osteoarticular disorders (40%), asthma (33.3%), hypertension (33.3%), infertility (35.7%), chronic venous insufficiency (28.6%), diabetes (26.7%), and dyslipidaemia (26.7%). Seven patients were randomized to the intervention group and 8 to the control group. Their baseline features are displayed in Table 2.

The first eight sessions took place between October 2019 and January 2020. Three participants dropped out before even starting the intervention (one travelled abroad, another one said the timing of the sessions was inconvenient, and the third did not give a specific reason). The rest attended between one and six sessions. Only five participants completed follow-up, three in the intervention and two in the control group. Of the ten patients not completing the programme, seven interrupted it due to early surgery. Unlike what was initially planned, because of the low attendance at the sessions, we decided to merge both treatment groups from session 2, since group intervention was not possible otherwise. The control group left after the standard session finished, whereas the intervention group joined the physiotherapist team thereafter.

The five participants completing the follow-up lost an average of 0.54 ± 5.2 kg (Intervention group +1.6 ± 4.3 kg; Control group −3.8 ± 5.7 kg) and the final BMI was 48.1 ± 7.6 kg/m^2^ (Intervention Group 45 ± 7.3 kg/m^2^; Control group 52.69 ± 10.6 kg/m^2^). Given the small sample size, no statistical analysis was performed and no conclusions can be drawn.

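### The programme is delivered in 10-person groups, separate by arm, but the detectable differences and named tests treat all 80 patients as independent

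*Protocol article*

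**What the plan says.** Randomization is by individual (Section 2.3): "Participants are assigned to their treatment group (ratio 1:1) following a computer-generated random sequence". Delivery is by group in both arms. The standard programme is "eight 2-h, fortnightly sessions, followed by 1-h monthly sessions until surgery" (Section 2.5), and the intervention arm adds half an hour of training after each 2-hour session (Section 2.6).

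Section 2.15 estimates that "we would be able to include 80 participants, 40 in each treatment arm". The same sentence gives the delivery arrangement behind that estimate: "following two 10 person groups (one control and one intervention) at a time". Section 2.5 separates the groups: "To avoid contamination between treatment arms, the control and intervention groups are scheduled every other week".

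The detectable difference in Section 2.15 rests on 80 patients, no loss to follow-up, a two-sided 5% level and an SD: "assuming a standard deviation in weight of 11 kg" gives 7 and 8 kg over 80–90% power, and "Assuming a standard deviation of 6 kg, as shown by other studies" gives about 4 kg. The tests named for comparing the arms are chi-squared, Student's t and Mann–Whitney U. The section mentions no ICC, design effect or session-group term.

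In the pilot the separation was abandoned (Section 3): "we decided to merge both treatment groups from session 2". Section 4 defends the shared arrangement. The planned changes listed there do not say which arrangement the main trial will use.

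**The concern.** Forty patients per arm in groups of 10 is about 4 groups per arm. Patients in one group go through education and cognitive-behavioural sessions together for 16 weeks, and Table 1 includes a group-dynamics activity. Peer influence could make their weight changes more alike than those of patients in different groups.

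When each group belongs to one arm only, that similarity adds to the variance of the difference between arms. A t-test on 80 individual values does not see it. The standard error is then too small, the false-positive rate exceeds 5%, and the difference detectable at a given power is larger than stated. This affects the primary outcome, change in body weight up to surgery.

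**Working it through.** **Inputs from the protocol article.** 40 patients per arm; groups of 10, hence 40/10 = 4 groups per arm and 8 in all; SD 11 kg or 6 kg; two-sided 5%; no loss (all Section 2.15).

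**Assumed.** ICC of 0.01, 0.02, 0.05 and 0.10, because the article gives none.

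**1. Reproduce the stated figures under independence.** Standard error at SD 11 kg = 11 × √(2/40) = 2.46 kg. By the normal approximation:
- 80% power: (1.960 + 0.842) × 2.46 = 6.9 kg
- 90% power: (1.960 + 1.282) × 2.46 = 8.0 kg

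With the noncentral t on 78 df these are 6.98 and 8.07 kg. SD 6 kg gives 3.8 and 4.4 kg. The stated 7, 8 and about 4 kg therefore correspond to a design effect of exactly 1. The like-for-like comparator at 80% power is 7.0 kg.

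**2. Separate sessions (Section 2.5).** Design effect DE = 1 + (10 − 1) × ICC. The true standard error is √DE times the one the t-test uses. Type I error = 2 × P(T₇₈ > 1.991/√DE). The detectable difference at 80% power and SD 11 kg is 6.98 × √DE on 78 df. The last column uses 6 df (8 groups minus 2 arms).

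| ICC | DE | √DE | Type I error | Detectable, 78 df | Detectable, 6 df |
|---|---|---|---|---|---|
| 0 | 1.00 | 1.00 | 5.0% | 7.0 kg | 8.3 kg |
| 0.01 | 1.09 | 1.04 | 6.0% | 7.3 kg | 8.7 kg |
| 0.02 | 1.18 | 1.09 | 7.1% | 7.6 kg | 9.0 kg |
| 0.05 | 1.45 | 1.20 | 10.2% | 8.4 kg | 10.0 kg |
| 0.10 | 1.90 | 1.38 | 15.3% | 9.6 kg | 11.4 kg |

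Simulation of 4 groups of 10 per arm (40,000 runs) gives type I errors of 6.0, 7.0, 10.5 and 15.5%, in agreement with the formula. The 6-df column is a worst case: moving from 78 to 6 df already raises 7.0 to 8.3 kg at ICC 0, before any clustering.

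**3. Shared sessions (as run in the pilot from session 2).** A group effect common to both arms cancels in the difference between arms, and the plain t-test becomes slightly conservative (about 4.6% at ICC 0.05 by simulation). What remains is clustering from the half-hour delivered to the intervention arm alone. With a group effect in that arm only, simulated type I error is about 6.1 / 7.6 / 10.4% at ICC 0.02 / 0.05 / 0.10. Averaging the two arms' design effects, (DE + 1)/2, gives nearly the same: 6.0 / 7.6 / 10.2%.

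**The case against.** **The ICC is not known.** Patients are randomized individually, so group effects can arise only through delivery. At ICC 0.01–0.02 the detectable difference moves from 7.0 to 7.3–7.6 kg, a 4–9% change. This stands: the direction is certain for any positive ICC with separate groups, but the size is not.

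**Groups may be smaller than 10 in practice.** Pilot attendance was poor, and much of the added intervention is home exercise. With groups of 5 at ICC 0.02, DE = 1 + 4 × 0.02 = 1.08 and type I error is 5.9%. This also stands, as a reason to show a range.

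**Calendar period and session leaders.** A reader might infer that these are further sources of clustering nested in arm. The article does not support that. One control and one intervention group run at the same time in alternate weeks, so period is shared between arms and largely cancels. No section says that leaders differ between groups. Peer effects within a group are what remains.

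**The group term may be in an analysis plan not shown.** The sentence naming the tests follows the baseline description and could be read as covering baseline comparisons only. That weakens any claim that the t-test is fixed as the primary analysis. It does not touch the detectable differences, which are stated in this article and allow for no clustering.

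**The pilot's merger is not a contradiction.** Section 3 discloses it as a departure from plan. What is open is the format of the main trial.

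**Conclusion.** The point holds conditionally. With separate 10-person groups as in Section 2.5, the stated 7, 8 and about 4 kg are too favourable for any positive within-group correlation. The effect is small at ICC 0.01–0.02 and material from about 0.05, where type I error is roughly double the nominal level and the 80%-power difference is 8.4 kg. These sizes assume full groups of 10, no loss and SD 11 kg.

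If the main trial keeps shared sessions, the inflation is smaller and comes only from the intervention arm's half-hour.

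A reader might conclude that the trial's intervals will certainly be too narrow, or that the true detectable difference is 8.7–11.4 kg. The article supports neither. The first needs a positive ICC and a session format that is not settled; the second is mostly the price of 6 degrees of freedom at the low end of the range. The point merits a change before the first cohort but does not undermine the design.

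**What to change.** 1. State before the first cohort whether the arms meet separately or share the standard session, and use one arrangement for all cohorts.
2. Record the session group each patient attends. Without that variable the correction may not be possible later.
3. For separate sessions, analyse weight change with a mixed model that has a random intercept for session group and small-sample degrees of freedom (Kenward–Roger or Satterthwaite). For shared sessions, use cohort as a block, with a group effect in the intervention arm only.
4. Restate the detectable difference over a declared ICC range, as in the table, keeping 80 patients.

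The cost is analysis wording and one recorded variable; no patient, visit or procedure is added. The downside is wider intervals and fewer degrees of freedom. With about 4 groups per arm, the between-group variance will also be poorly estimated.

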The pilot study has indeed led us to reflect on the possible causes of low acceptance of and adherence to the programme, as well as establishing mechanisms to overcome this. Seventy percent of the participants were operated on before the group intervention was completed. Therefore, coordination between the medical and surgical teams is needed, to improve the timing of the treatment. Indeed, patients who are further down on the waiting list will be invited to participate, in coordination with the Surgery Department. Moreover, additional measures are planned to improve motivation and acceptance of and adherence to the programme. More information about the group intervention will be given to patients when they are referred to our centre for bariatric surgery. An informative leaflet is being designed by the Endocrinology and Surgery Departments and will be explained and given to the patients in their first visit to them. The inclusion of this kind of approach in the routine care of patients with obesity should increase its acceptability. Alternative scheduling, or a combination of physical and online sessions, might also improve adherence in the case these measures are insufficient. These changes to the protocol will be submitted to the Ethics Committee.

The main strength of our study is the multidisciplinary approach of the intervention, which includes not only nutritional, behavioural, and psychological interventions, but also physical conditioning and respiratory training. The fact that it is designed as a randomized, controlled trial sets high expectations regarding the quality of the results. Once the SARS-CoV-2 allows, the clinical trial will start.

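### The detectable differences of 7–8 kg and about 4 kg hold only with no loss to follow-up, and this premise was not revisited after a pilot in which 5 of 15 completed

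*Protocol article*

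**What the plan says.** Section 2.15 (Statistical Analyses) takes the sample size from expected recruitment over one year: "we would be able to include 80 participants, 40 in each treatment arm". It then states what that number can detect: "The inclusion of 80 participants, without any loss to follow-up, assuming a standard deviation in weight of 11 kg", "for a two-tailed *p* < 0.05", would allow a difference "with 80–90% statistical power, of 8 and 7 kg to be detected, respectively". With an SD of 6 kg the detectable difference is put at around 4 kg. The analysis is by intention to treat, with missing values filled by last observation carried forward.

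Section 2.7 (Outcomes) defines the primary outcome as weight change from the start of the programme to the time of surgery.

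Section 3 (Results) reports 15 randomised in the pilot. "Only five participants completed follow-up, three in the intervention and two in the control group". Seven of the ten non-completers stopped because surgery came early. Three participants dropped out before starting. Weight change is reported for the five completers only.

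Section 4 (Discussion) classes the non-completers as losses to follow-up and names low adherence as the main limitation. It lists measures to improve timing and adherence, but gives no expected loss rate, no revised sample size and no revised detectable difference. It also says: "Seventy percent of the participants were operated on before the group intervention was completed".

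**The concern.** The only statement of what the trial can detect rests on every randomised patient supplying the primary outcome. The same article reports a pilot of the same programme in which two thirds did not complete follow-up, and it leaves the statement unchanged while announcing that the main trial will start. Readers would then judge the design, and later any null result, against a sensitivity that holds only in a case the pilot did not come near.

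The planned imputation might seem to protect the calculation because it keeps 40 per arm in the analysis. It does not: a carried-forward value adds a patient to the count without adding information about weight at surgery.

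**Working it through.** **Inputs.** 40 per arm, two-sided 0.05, SD 11 or 6 kg, power 80% and 90% (section 2.15); 15 randomised, 5 completers, 7 early operations (section 3). That the remaining three non-completers are the three who dropped out before the start is inferred from the counts (10 − 7 = 3).

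**Step 1: reproduce the stated figures.** Detectable difference = (z for 0.975 + z for power) × SD × √(2/n per arm).

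- SD 11, 80%: (1.960 + 0.842) × 11 × √(2/40) = 6.89 kg; noncentral t 6.98 kg.
- SD 11, 90%: (1.960 + 1.282) × 11 × √(2/40) = 7.97 kg; noncentral t 8.07 kg.
- SD 6: 3.76 and 4.35 kg; noncentral t 3.81 and 4.40 kg.

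So 7–8 kg and about 4 kg are right for zero loss. The printed pairing is reversed: 80% power goes with 7 kg and 90% with 8 kg. Read as printed, 8 kg at 80% would need 60 patients and 7 kg at 90% would need 104.

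**Step 2: loss rates from the pilot.**

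- 3/15 = 20%: weight at surgery is recorded for everyone operated on early, and only the three drop-outs before the start are unobserved. 40 × 0.80 = 32 per arm.
- 10/15 = 67%: only completers supply a weight, as in the pilot report. 40 × 1/3 = 13.3, taken as 13 per arm. The exact 95% confidence interval for 10/15 is 38–88%.

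**Step 3: detectable difference from observed weights (noncentral t, 80% / 90% power).**

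| Observed per arm | SD 11 kg | SD 6 kg | Power for 7 kg, SD 11 |
|---|---|---|---|
| 40 (no loss) | 7.0 / 8.1 kg | 3.8 / 4.4 kg | 80% |
| 32 (20% loss) | 7.8 / 9.1 kg | 4.3 / 4.9 kg | 71% |
| 13 (67% loss) | 12.6 / 14.6 kg | 6.9 / 8.0 kg | 34% |

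Using 13.33 instead of 13 per arm gives 12.4 / 14.4 kg at SD 11, so the rounding matters little.

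**Step 4: does carrying values forward help?** As an illustration, assume lost patients carry their baseline weight forward (zero change) in both arms, and a fraction r is observed. The expected difference becomes r × d.

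- SD held at 11 kg: 7 kg shrinks to 0.8 × 7 = 5.6 kg (power 62%, normal approximation) or 7/3 = 2.3 kg (16%). This is pessimistic, because zero changes also reduce the SD.
- SD allowed to shrink to 11 × √r (the most it can, when mean changes are near zero): the standardised difference is r × d / (11 × √r × √(2/40)) = d / (11 × √(2/(40r))), which is exactly the observed-only expression with 40r per arm. For r = 0.8 and d = 7: 5.6/2.20 = 2.55, and 7/2.75 = 2.55, against 7/2.46 = 2.85 with no loss.

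Under this assumption, carrying forward does about as well as analysing the observed patients, or worse. It does not return the power to 80%. Carrying a later weight instead of baseline would dilute less.

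**Step 5: the 70% figure.** 7/10 = 70% of non-completers; 7/15 = 47% of participants.

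**The case against.** The zero-loss condition is printed openly and the estimate is dated to the design stage, before the pilot. Nothing is concealed: the losses are reported, discussed as the main limitation and met with planned measures. A reader might infer that 7–8 kg is a miscalculation; step 1 shows that it is not. Apart from the reversed order, this objection stands. What remains is a premise left in place after the article's own data contradicted it.

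The pilot is small and its main cause of loss is the one the plan targets. Seven of ten losses came from early surgery, and patients further down the waiting list will now be invited. A reader might infer that the main trial will lose two thirds of its patients, or needs several times as many. The article does not support that; 67% is a worst case with a wide interval. Yet even the lower limit, 38%, is far from zero.

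A patient operated on early has reached the time point that section 2.7 defines, so that weight need not be lost. This is the strongest objection and it stands. It is why the lower bound is 20%, and why the fix turns on recording that weight. Against it, the Discussion itself counts these patients as lost, and the pilot gives weight change for completers only.

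A reader might also take 7/15 (47%) as an intermediate loss rate. It fits neither case: it treats the early operations as lost but the three drop-outs as observed.

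Finally, with SD 6 the worst case gives 6.9 / 8.0 kg, numerically the stated 7–8 kg. But then the article's claim for SD 6, around 4 kg, is the one that fails.

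**Conclusion.** The point holds in a limited form. The stated sensitivity is correct for 80 observed patients and for no smaller number, and the article gives no reason to expect 80. With the pilot's losses as bounds, the detectable difference at SD 11 lies between 7.8 / 9.1 kg (20% loss) and 12.6 / 14.6 kg (67% loss) at 80% / 90% power. At SD 6 it lies between 4.3 / 4.9 kg and 6.9 / 8.0 kg. Power for 7 kg at SD 11 is 71% or 34% instead of 80%. At the favourable bound the shortfall is modest; most of the distance between the bounds depends on whether weight at surgery is collected from patients operated on early.

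The results assume equal loss in both arms, losses unrelated to outcome, the article's own SDs and an analysis of observed weights. The 20% bound treats the three drop-outs before the start as unobserved; weighing them at surgery too would improve on it.

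The 70% statement in the Discussion is a separate, minor wording error. It does not enter the power calculation.

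**What to change.** In section 2.15, before the main trial starts:

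1. Keep 80 randomised, and restate the detectable difference for the number expected to contribute an observed weight, at 80% / 90% power. At 20% loss: 7.8 / 9.1 kg (SD 11) and 4.3 / 4.9 kg (SD 6). At 67% loss, labelled as the pilot worst case (95% CI 38–88%): 12.6 / 14.6 kg and 6.9 / 8.0 kg. The zero-loss figure may stay as a reference, but not as the only basis.
2. In the same sentence, correct the order: 80% power with 7 kg, 90% with 8 kg.
3. State that weight at surgery counts as the primary outcome for all randomised patients, whether or not they complete the programme. This follows from the endpoint definition in section 2.7.

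In section 4, change the 70% statement to 70% of non-completers (7/10), or 47% of participants (7/15).

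The cost is a few sentences, the recording of one weight per operated patient and a less favourable stated figure. No extra patients are needed, and the article already says that protocol changes will go to the Ethics Committee.

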### 2.7. Outcomes

The primary outcome is the change in body weight between the start of the programme and the time of surgery.

Secondary outcomes include: changes in body composition, comorbidities, changes in eating behaviours, health-related quality of life, functional capacity, length of hospital stay after surgery and short-term complications of surgery.

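### The two detectable differences in the power statement are transposed: at 40 per arm and SD 11 kg, 7 kg goes with about 80% power and 8 kg with about 90%

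*Protocol article*

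**What the plan says.** All the inputs stand in section 2.15 (Statistical Analyses) of the protocol article. The trial expects "80 participants, 40 in each treatment arm", a number the section derives from one year's recruitment capacity. The calculation is made "without any loss to follow-up", "assuming a standard deviation in weight of 11 kg" (citing reference [16]) and "for a two-tailed *p* < 0.05". The result is that this sample "would allow a difference between groups, with 80–90% statistical power, of 8 and 7 kg to be detected, respectively".

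A second scenario follows: "Assuming a standard deviation of 6 kg, as shown by other studies [64], the detectable difference would be reduced to around 4 kg".

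Section 2.7 (Outcomes) defines the endpoint to which the calculation should apply: "The primary outcome is the change in body weight between the start of the programme and the time of surgery".

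**The concern.** The sentence lists power in rising order (80, then 90) and differences in falling order (8, then 7), and its last word ties them together one to one. The reader is told that 8 kg is detectable with 80% power and 7 kg with 90%. That ordering cannot be right: with everything else fixed, power rises with the size of the true difference.

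The direction of the error matters. The smaller effect is given the more favourable power. Someone who later interprets a null result could take the plan to say that, at an SD of 11 kg, a true 7 kg difference would be missed one time in ten, when the stated inputs give about one time in five.

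A smaller point sits beside it. The 11 kg is described as an SD in weight, but the primary outcome is a change in weight. The two quantities can differ considerably, and the calculation is relevant to the endpoint only if 11 kg describes the change.

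**Working it through.** **Inputs, all from section 2.15:** n = 40 per arm, SD = 11 kg, two-sided α = 0.05, no loss to follow-up, comparison of two means by Student's t (one of the tests the section lists).

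**Standard error of the difference:** SD × √(2/n) = 11 × √(2/40) = 11 × 0.2236 = 2.460 kg.

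**Step 1: detectable difference at each power.** Normal approximation: (z for α/2 + z for power) × standard error.
- 80% power: (1.960 + 0.842) × 2.460 = 6.89 kg
- 90% power: (1.960 + 1.282) × 2.460 = 7.97 kg

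The exact calculation with the noncentral t on 78 degrees of freedom gives 6.98 kg and 8.07 kg. Rounded, these are 7 and 8 kg, in the opposite order to the printed one.

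**Step 2: power at each stated difference.** Normal approximation: Φ(difference / standard error − 1.960).

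| Difference | Power implied by the text | Normal approximation | t-test, 78 df |
|---|---|---|---|
| 7 kg | 90% | Φ(2.846 − 1.960) = 81.2% | 80.3% |
| 8 kg | 80% | Φ(3.252 − 1.960) = 90.2% | 89.5% |

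As printed, each pairing is off by about 9 to 10 percentage points. With the two differences swapped, both agree with the stated power to within about 1 point.

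**Step 3: could another reading rescue the printed order?** A one-sided 0.05 test gives 88.0% at 7 kg and 94.3% at 8 kg (t-test). That does not fit either, and the text specifies two tails. No choice of test or approximation can give the smaller difference the higher power.

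**Step 4: what the printed pairing would require.** Normal approximation: n per arm = 2 × [(sum of z values) × 11 / difference]².
- 7 kg at 90%: 2 × (3.242 × 11 / 7)² = 51.9, so 52 per arm
- 8 kg at 80%: 2 × (2.802 × 11 / 8)² = 29.7, so 30 per arm

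Neither is 40. For the swapped pairs, the same formula gives 39 per arm (7 kg at 80%) and 40 per arm (8 kg at 90%). This match identifies the fault as a transposition, not a hidden assumption.

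**Step 5: the SD 6 kg line.** Standard error = 6 × 0.2236 = 1.342 kg. The detectable difference is 3.76 kg at 80% and 4.35 kg at 90% by the normal approximation (3.81 and 4.40 kg by t). A 4 kg difference has 84.6% power (83.8% by t). The stated value of around 4 kg is correct.

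**Step 6: the SD label.** Table 2 gives pilot baseline weight SDs of 19.5 kg (n = 7) and 23.2 kg (n = 8). The Results give an SD of weight change of 5.2 kg over five completers. The 11 kg is roughly half of the former (11/19.5 = 0.56; 11/23.2 = 0.47) and about twice the latter (11/5.2 = 2.1). The pilot matches it under neither description.

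**The case against.** The strongest counter-argument is about consequence. The 80 participants came from recruitment capacity, and the detectable differences were worked out afterwards. Putting them in the right order changes neither the sample size nor the allocation, endpoint or test. The two values are also correct as a set, and a careful reader may spot the swap. All of this is true and limits the damage. It does not make the sentence right: it still claims a power for 7 kg that its own inputs do not deliver.

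Three stronger readings are tempting, and the article does not support them.

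- **That the design as such misses a 7 kg difference 20% of the time.** This holds only at an SD of 11 kg. Under the plan's own 6 kg scenario, 7 kg is 7 / 1.342 = 5.2 standard errors, and power exceeds 99%.
- **That 11 kg can only be an SD of change.** The pilot baseline SDs make an SD of body weight look unlikely, but they come from 7 and 8 patients. The 5.2 kg comes from five completers and pools two arms whose mean changes differ (+1.6 and −3.8 kg), and the authors draw no conclusions from these data. Reference [16] is not at hand. The label does not match the endpoint; what the figure really measures stays open.
- **That the trial needs more participants.** The 52 per arm in the working shows what the printed pairing would require. The plan does not commit to 90% power at 7 kg as a design target.

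**Conclusion.** The power sentence is wrong as written and needs correcting. With 40 per arm, SD 11 kg, two-sided 0.05 and complete follow-up, a 7 kg difference has about 80% power (80.3% by t-test) where the text implies 90%, and an 8 kg difference has about 90% (89.5%) where the text implies 80%. The type II error at 7 kg is then about 20%, twice the implied 10%. That doubling is conditional on the 11 kg SD and on the plan's assumption of no losses.

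The ordering error itself depends on no assumption, since power cannot fall as the difference grows. Nothing elsewhere in the article corrects it. The SD 6 kg statement is sound. The SD label is a matter for clarification, not a demonstrated error in the value.

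**What to change.** Restate the result in section 2.15 along these lines: with 80 participants (40 per arm), no loss to follow-up, an SD of 11 kg and a two-sided 5% test, the trial can detect a between-group difference of 7 kg with 80% power and 8 kg with 90% power. Leave the SD 6 kg sentence as it is.

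In the same edit, check in reference [16] whether 11 kg is the SD of the change in weight. If it is, say so. If it is the SD of body weight, state that, and say why it is used for an endpoint defined as a change.

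The cost is one sentence and one look at a cited source. No participants are added and no design element changes; the only loss is a less favourable power figure for 7 kg. The Discussion says that the trial has yet to start and that protocol changes will go to the Ethics Committee, so the correction can go in with them.
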